## 5. Sample Size Estimation, Statistical Methods, and Reporting Results

### 5.1. Sample Size Estimation

A total of 60 participants will be recruited. The estimation of sample size was based on 80% statistical power regarding one of the primary variables, overall sleep quality (PDSS-2 total score). In our preliminary study, we observed a significant change after Qigong exercise in overall sleep quality by 11.5 points between two groups (experimental vs. control). A pooled standard deviation between two groups was 10.7. With a statistical power of 80% and a Type I error rate at 0.05, the estimated sample size was 14 for each group. Considering a potential dropout rate of 30%, the estimated sample size is 20 for each group. However, this sample size may not have enough statistical power for testing secondary hypotheses related to variables of other non-motor symptoms and/or serum biomarkers. Therefore, we propose to enroll 30 participants in each of the intervention arms.

### 5.2. Statistical Analysis

Descriptive statistics including mean, standard deviation, frequency, and percentage will be calculated. Mean changes between the three-time points (baseline, post-intervention, and 6-month follow-up) in the experimental and control groups will be examined by two-way mixed-design analysis of variance (ANOVA). If no significant interaction is observed, the main effect will be analyzed using two-tailed t-tests with Bonferroni correction for groups and repeated measures ANOVA for time. Correlation coefficients (r) will be utilized to find relationships between variables including non-motor symptoms and inflammatory biomarker levels. Duration of PD will be used as a covariate in the analysis. The level of significance is set at 0.05. In addition, sub-group analysis based on demographic (e.g., sex and age) or clinical (e.g., Hoehn and Yahr stage and disease duration) information will be conducted.

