### 2.2. Specific Aims

Specific aim I. To examine the effects of Qigong exercise on non-motor symptoms in PD.

Primary hypothesis: Participants will have greater improvement in sleep quality after Qigong exercise than the participants after sham Qigong exercise.

Secondary hypothesis I: Participants will have greater improvement in cognitive function, fatigue, anxiety, depression, overall non-motor symptoms, and quality of life after Qigong exercise than the participants after sham Qigong exercise.

Specific aim II. To examine changes in inflammatory biomarkers in serum after practicing Qigong exercise.

Secondary hypothesis II: Participants will have greater reduction in levels of inflammatory biomarkers (IL-1β, IL-6, and TNF-α) after Qigong exercise than the participants after sham Qigong exercise.

Specific aim III. To examine relationships between changes in non-motor symptom scores and changes in the inflammatory status in PD after the intervention (both Qigong and sham Qigong).

Secondary hypothesis III: Changes in non-motor symptom scores will significantly correlate with changes in levels of the inflammatory biomarkers.

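### Aim III reads as a correlation across both arms with no term for arm, so arm effects on both sleep and cytokines would inflate its false-positive rate

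*Protocol article*

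**What the plan says.** Section 2.2 (Specific Aims) sets Aim III as the relation between changes in symptom scores and "changes in the inflammatory status in PD after the intervention (both Qigong and sham Qigong", the last words standing in a parenthesis. Secondary hypothesis III predicts a positive test result: "Changes in non-motor symptom scores will significantly correlate with changes in levels of the inflammatory biomarkers".

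Section 5.2 (Statistical Analysis) gives the method in one sentence: "Correlation coefficients (r) will be utilized to find relationships between variables including non-motor symptoms and inflammatory biomarker levels". It then adds "Duration of PD will be used as a covariate in the analysis" and "The level of significance is set at 0.05". Treatment arm is not mentioned in connection with the correlations, and neither are within-arm coefficients.

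Section 2.2 also hypothesises that Qigong will beat sham on sleep quality (primary hypothesis) and on IL-1β, IL-6 and TNF-α (Secondary hypothesis II).

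**The concern.** Aim III is meant to show that patients whose inflammation falls more are also those whose symptoms improve more. A correlation across both arms mixes that question with a different one: whether the arms differ on both variables. If Qigong lowers both PDSS-2 and a cytokine, the Qigong patients sit lower on both axes and the sham patients higher. The two clusters alone give a positive r, even if the two changes are unrelated among the patients of each arm.

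At stake is the mechanistic reading. The Introduction proposes an inflammatory pathway, and the Discussion says the trial will uncover the relation between symptoms and inflammatory status. A pooled r adds little to that if part of it only repeats the results of Aims I and II. The bias arises in the very case where the treatment works on both variables. The primary sleep comparison is not affected.

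**Working it through.** **Inputs from the protocol article**
- Between-arm PDSS-2 effect 11.5 points, pooled SD 10.7 (section 5.1): d₁ = 11.5/10.7 = 1.07.
- 30 patients per arm, 1:1 allocation (sections 5.1 and 2.7): N = 60. With the 30% dropout of section 5.1, 60 × 0.70 = 42.
- Level 0.05 (section 5.2).

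**Assumptions**
- The article gives no between-arm cytokine effect, so d₂ is assumed and varied over 0, 0.3, 0.5, 0.8 and 1.0.
- The SD of 10.7 is taken to apply to the PDSS-2 change. Section 5.1 does not say so, and d₁ = 0.5 is therefore run as well.
- The correlation test is taken as two-sided. Section 5.2 says this only for the "two-tailed t-tests with Bonferroni correction for groups".
- Changes are normal with equal variance, and their correlation within each arm is zero.

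**The plan's own figure.** Section 5.1 states: "With a statistical power of 80% and a Type I error rate at 0.05, the estimated sample size was 14 for each group". The normal formula gives 2 × (1.960 + 0.842)² × (10.7/11.5)² = 13.59, so 14 per group, and 14/0.70 = 20 after dropout. Both figures reproduce (a t-based calculation gives 14.6, so 15, a trivial difference). No design figure is stated for Aim III.

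**Correlation produced by arm alone.** With 1:1 allocation and zero within-arm correlation,

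r = (d₁d₂/4) / √[(1 + d₁²/4)(1 + d₂²/4)].

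For d₁ = 1.07 and d₂ = 1.0: 0.269 / √(1.289 × 1.25) = 0.269/1.269 = 0.21. For d₂ = 0.8, 0.5 and 0.3 the same formula gives 0.18, 0.12 and 0.07. For d₂ = 0 it gives 0.

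**False-positive rate of the pooled test** (20,000 simulated trials per setting):

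| Sleep d₁ | Cytokine d₂ (assumed) | N = 60 | N = 42 |
|---|---|---|---|
| 1.07 | 0 | 5% | 5% |
| 1.07 | 0.3 | 8% | 7% |
| 1.07 | 0.5 | 14% | 11% |
| 1.07 | 0.8 | 28% | 20% |
| 1.07 | 1.0 | 38% | 28% |
| 0.5 | 0.3 to 1.0 | 6% to 13% | 5% to 11% |

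**Does the named covariate help?** No. Under randomisation PD duration is independent of arm, so removing it leaves the arm difference in place. At d₁ = 1.07, d₂ = 1.0 and N = 60, the rate is 37% with PD duration adjusted and 38% without.

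**Does arm adjustment help?** Yes. With arm removed from both changes, the rejection rate was 4.8% to 5.6% in every setting run.

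**The case against.** The strongest objection is that pooling is inferred. The parenthesis in section 2.2 qualifies the intervention. It can mean one coefficient over everyone or one coefficient in each arm. Section 5.2 does not decide between them, and in a condensed article such detail may sit in an analysis plan that is not shown. This stands as a limit on certainty. But the article does state the population, the statistic, the level and a covariate for the analysis, and arm is not among them. The reading that combines the arms is the natural one, and it is the one that misleads.

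A second objection is that the relation is secondary, and the Introduction calls this part of the study exploratory. That bears on the weight of the point. Section 2.2 nevertheless makes it a hypothesis judged by significance.

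Four stronger readings are tempting, and the document does not support them:
- *The correlation will come out significant whenever Aims I and II succeed.* It usually will not. Even among simulated trials in which both arm comparisons reach p < 0.05 (d₁ = 1.07, d₂ from 0.3 to 1.0), the spurious r is significant in roughly 20% to 39% with 60 patients and 19% to 32% with 42.
- *The pilot TNF-α result supplies a large cytokine effect.* The Introduction gives a fall from 13.8 ± 0.6 to 12.3 ± 1.6 over time, with no control-arm figure. That is not a between-arm difference in change.
- *The analysis ignores covariates altogether.* PD duration is named, though the text does not say whether it applies to the correlations. It would not remove this bias in any case.
- *Section 5.2 correlates levels where the hypothesis concerns changes.* The Introduction, Aim III and Secondary hypothesis III all speak of changes. The wording in section 5.2 is generic shorthand and not a competing definition.

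**Conclusion.** The point holds as a bias that the plan does not guard against, not as a certain false finding. Read naturally, Aim III tests a both-arm correlation without arm. Its false-positive rate, against zero correlation within arms, lies between about 7% and 38% for the protocol's sleep effect and assumed cytokine effects of 0.3 to 1.0. It is 5% to 13% if the sleep effect is d = 0.5, and nominal if arm affects only one of the two variables. The size therefore depends on a cytokine effect that the document does not give, and on the arms being pooled. If a separate coefficient per arm is intended, the problem disappears and one sentence should say so. The null examined here is no correlation among patients within an arm. Each patient contributes a single pair of changes, so nothing is shown about association within a patient. This is a cheap improvement to a secondary analysis.

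**What to change.** State in section 5.2 that Aim III uses a partial correlation, or a regression of symptom change on biomarker change, with randomised arm as a term in addition to PD duration. Report the within-arm coefficients alongside. Base Secondary hypothesis III on the arm-adjusted estimate with its 95% CI. The arm term is the essential part: it alone brought the error rate back to about 5%, and further adjustment is not needed for this purpose.

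The cost is a change of wording and about one degree of freedom, with no extra patients, visits or assays. The sponsor also accepts a correlation that may look smaller than the pooled one.

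### The three-visit interaction test of PDSS-2 does not match the single two-group comparison that the trial hypothesises and is sized for; a baseline-adjusted post-intervention contrast would

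*Protocol article*

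**What the plan says.** Section 2.2 states the primary hypothesis as one directional comparison of two arms: "Participants will have greater improvement in sleep quality after Qigong exercise than the participants after sham Qigong exercise". It names no visit.

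Section 5.1 sizes the trial on one two-group difference: "we observed a significant change after Qigong exercise in overall sleep quality by 11.5 points between two groups", with a pooled SD of 10.7. It concludes: "With a statistical power of 80% and a Type I error rate at 0.05, the estimated sample size was 14 for each group". That becomes 20 per group for 30% dropout, and 30 per group are enrolled to help the secondary hypotheses.

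Section 5.2 sets the analysis. "Mean changes between the three-time points (baseline, post-intervention, and 6-month follow-up) in the experimental and control groups" are examined by a two-way mixed-design ANOVA. The next step is conditional: "If no significant interaction is observed, the main effect will be analyzed using two-tailed t-tests with Bonferroni correction for groups", with repeated-measures ANOVA for time. On covariates it says "Duration of PD will be used as a covariate in the analysis", and on the error rate "The level of significance is set at 0.05". Baseline PDSS-2 is collected from everyone (Section 2.1) but enters only as one of the three repeated levels.

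**The concern.** The hypothesis and the sample size are 1-df, two-group comparisons. The test that would deliver the treatment result is a 2-df, non-directional interaction over three visits, and Section 5.1 gives no calculation for it. A significant interaction says that the arms follow different profiles. It does not say that they differ at the end of the 12-week intervention, because an effect that exists only at 6 months also produces one. The last visit comes six months after the group programme ends.

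The fallback does not repair this. In this model the group main effect is the arm difference averaged over all three visits. One of them is baseline, where randomisation makes the expected difference zero, so a sustained effect is diluted to two thirds.

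The named covariate helps little. Disease duration at entry is fixed within a person, so as a main effect it leaves the within-person error term of the interaction unchanged. Baseline PDSS-2, which is already collected, could be used as a covariate and is not.

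**Working it through.** **Inputs from the article.** Difference 11.5, SD 10.7, power 80%, alpha 0.05, dropout 30%, 30 enrolled per arm (Section 5.1); two-tailed testing (Section 5.2).

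**Assumptions not in the article.** Between-visit correlation ρ from 0.3 to 0.8, equal between all visits (compound symmetry); 10.7 read as the SD of the score; a smaller true effect of 7 points; a fraction c of the effect retained at 6 months.

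**1. The plan's own figure.** n = 2(1.960 + 0.842)² × 10.7² / 11.5² = 13.59, so 14 per group. 14 / 0.70 = 20. Both reproduce. Enrolling 30 leaves 30 × 0.70 = 21 completers per arm.

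**2. Interaction test.** The arm differences over the visits are (0, d, c·d), and S is their sum of squares about their mean. The noncentrality is (n/2)·S / [SD²(1−ρ)], on 2 and 2(2n−2) df. For d = 7: S = 32.67 at c = 1, 24.5 at c = 0.5 and 32.67 at c = 0. The minimum is at c = 0.5, so half retention is this test's worst case, and complete fading gives the same power as full retention.

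**3. Post-intervention ANCOVA.** The noncentrality is (n/2)·d² / [SD²(1−ρ²)], on 1 and 2n−3 df. It does not depend on c.

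At n = 21, d = 7, ρ = 0.5:
- ANCOVA: 10.5 × 49 / (114.49 × 0.75) = 5.99.
- Interaction, sustained: 10.5 × 32.67 / (114.49 × 0.5) = 5.99.

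The two are equal here, so the power gap at ρ = 0.5 comes from spending two numerator df instead of one.

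**4. Power, 21 per arm, d = 7.**

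| ρ | ANCOVA | Interaction, sustained | Interaction, half retained |
|---|---|---|---|
| 0.5 | 66.5% | 56.6% | 44.5% |
| 0.7 | 82.5% | 79.9% | 66.9% |
| 0.8 | 93.1% | 93.5% | 84.6% |

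**5. Planned effect, d = 11.5, sustained (ANCOVA against interaction).**
- 30 per arm: 99.0% against 95.8% at ρ = 0.3; 99.7% against 99.3% at ρ = 0.5; both about 100% at ρ = 0.7.
- 21 per arm: 94.5% against 85.7% at ρ = 0.3; 97.5% against 95.2% at ρ = 0.5.
- With half retention, 21 per arm and ρ = 0.5: 97.5% against 87.4%.

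**6. Where the proposed test loses (21 per arm, d = 7, ρ = 0.5).**
- Effect 1.25 times as large at 6 months: interaction 69%, ANCOVA 66%.
- Effect 1.5 times as large: interaction 82%, ANCOVA 66%.
- A 7-point effect only at 6 months: S is again 32.67, so interaction 57%, while the post-intervention ANCOVA has only its 5% error rate.

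**7. Fallback group effect.** A sustained effect becomes 2d/3 = 4.67, and the variance of a person's three-visit mean is SD²(1+2ρ)/3 = 76.3 at ρ = 0.5. The noncentrality is 10.5 × 4.67² / 76.3 = 3.0, which gives 39% power. If a significant interaction or a significant group effect would each count as success, simulation under no effect puts the type I error at about 9.5%.

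**8. If 10.7 is the SD of change** (21 per arm, d = 7). The interaction test has 57% (sustained) or 45% (half retained) at any ρ. ANCOVA has 66.5%, 61% and 59% at ρ = 0.5, 0.7 and 0.8.

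**The case against.** The best defence is that the planned test is valid and suits a three-visit design. Section 2.2 names no visit, so testing the whole profile is a legitimate reading, and taking post-intervention as primary is an inference from the 12-week programme and the sizing. Section 3.1 asks Qigong participants to keep practising twice daily after week 12, so an effect that grows is plausible, and the interaction test would then be stronger. Baseline is not ignored either: as a level of the within-person factor, it takes chance imbalance out of the interaction. All of this stands.

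A reader might infer that ANCOVA gives more power at no cost, or that the trial is underpowered as planned. The article supports neither. It gives no correlation, no retention figure and no 7-point effect. The tests tie near ρ = 0.8 with a sustained effect, and at the planned 11.5 points with 30 per arm both exceed 95% for ρ of 0.3 or more. Nor does fading as such cost the interaction test power, since complete fading matches full retention.

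It can also be said that follow-up contrasts and covariate coding belong in an analysis plan that is not shown. That is fair for the detail: a covariate-by-time term would enter the interaction model, and a Bonferroni correction with only two arms may mean visit-wise t-tests rather than a true group main effect. It does not dispose of the point, because Section 5.2 commits to a particular test and fallback, and these do not match Sections 2.2 and 5.1.

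**Conclusion.** The mismatch stands. The article hypothesises and sizes one two-group difference, then plans a 2-df interaction that cannot locate a difference at the post-intervention visit, with a fallback that dilutes it. This should be changed, mainly so that the result answers the question asked.

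The efficiency gain is a secondary and conditional reason. It is moderate for effects below the planning value at moderate correlation, small at the planning value with 30 per arm, and negative if the effect builds after week 12. The figures rest on the assumed effect, correlation, SD reading and covariance pattern listed above.

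**What to change.** State in Section 5.2 that the primary analysis is the between-arm difference in PDSS-2 total at the post-intervention visit, adjusted for baseline PDSS-2. Use ANCOVA, or the matching contrast of a repeated-measures model with baseline as covariate. Disease duration may stay as a further covariate. Report the estimate with its 95% CI beside the −3.44-point MCID cited in Section 4.2. Make the 6-month contrast secondary, and drop the step from interaction to main effects for the primary outcome. If the sponsor's main interest is in fact 6 months or the whole profile, say so and name that contrast instead.

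Baseline adjustment may be extended to the secondary clinical scores, but not automatically to the biomarkers. The pilot TNF-α means of 13.8 and 12.3 (Introduction) lie below the 15.6 pg/mL lower limit of the TNF-α kit (Section 4.3), if they are in the same unit, and values below the assay range need their own method.

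The change is to wording only: no added participants, visits or measurements. The price is less power for the primary test if the benefit grows or first appears after week 12.

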### 5.3. Reporting Results

Study results will be reported under the Consolidated Standards of Reporting Trials (CONSORT) guidelines.

## 6. Discussion

This study protocol is designed to investigate the efficacy of Qigong exercise on non-motor symptoms and inflammatory status in individuals with PD. Qigong exercise has shown benefits in a variety of medical conditions [17,24,46,47,48,49]. However, to our knowledge, only a few studies, including our own, have examined the efficacy or effectiveness of Qigong exercise in improving non-motor symptoms such as sleep disturbance, cognitive decline, fatigue, pain, mood, and quality of life, as well as inflammatory status in the PD population [16,17,18,26,27].

Complementary and alternative medicine originating outside of conventional Western medicine is generally well-received among individuals with various medical conditions as well as healthy people. Particularly, the use of a mind-body intervention including yoga, Tai Chi, and Qigong gradually increased from 2002 to 2012, according to the United States national health statistics reports [50]. Despite that many people have benefited by complementary and alternative medicine, a lack of clinical research is one of the largest barriers for the clinical use of complementary approaches.

This study will offer a foundation for a future multi-center RCT to identify the effectiveness of Qigong exercise and will contribute to the development of a novel, safe, and cost-effective approach for individuals with PD. In addition, the study will examine the changes in inflammatory status induced by Qigong exercise in PD, providing a better understanding of the role of inflammation in PD, and will uncover the relationship between non-motor symptoms and inflammatory status in PD.

## Figures and Tables

**Figure 1 medicines-06-00013-f001:**
[figure not shown]
Study flow chart. A screening will be conducted using the screening tool developed by our research laboratory (Table A1). A study participation consent will be obtained and a baseline assessment will be conducted at the initial visit. After group randomization, participants will be assigned into either experimental or control groups. Throughout a 12-week intervention, participants will perform the intervention exercise twice a day at home and attend a total of 9 group meetings (weekly meeting for first 6 weeks and then biweekly meeting for next 6 weeks). After completing the 12-week intervention, a post-intervention assessment will be conducted within 2 weeks after the 12-week intervention. A follow-up assessment will be conducted 6 months after the completion of 12-week intervention.

**Table 1 medicines-06-00013-t001:** Inclusion and exclusion criteria and rationale.

Criteria	Rationale
Inclusion Criteria	
Idiopathic PD	Individuals who had been diagnosed based on the United Kingdom Parkinson’s Disease Brain Bank Society diagnostic criteria are included to establish a diagnostic baseline.
Women and men aged 40 to 75 years	Clinically, PD is not common in young individuals. In addition, individuals older than 75 years are more likely to have comorbidities or be on an advanced stage of PD, which may confound the study results.
Current use of levodopa	Levodopa is a standard medication for PD.
Stable levodopa dose	Changes in levodopa dosage may cause difficulties to determine whether the expected benefits are caused by the changed medication dose or the intervention.
Hoehn and Yahr stage I to III	Hoehn and Yahr stage above III involves significant motor impairment, which may restrict individual’s movement during exercise.
Exclusion Criteria	
Mini Mental State Examination <24	Less than score 24 on Mini Mental State Examination indicates cognitive impairment. Those individuals scored under 24 may have difficulties to follow study instructions.
Other neurological disease including other forms of parkinsonism, uncontrolled or significant cardiovascular diseases, orthopedic or medical problems	Other neurological conditions may confound the study results. Uncontrolled or significant cardiovascular conditions and orthopedic conditions may cause unwanted events during the exercise.
History of major head trauma with loss of consciousness	Qigong involves meditation. Individuals with head related injuries may have difficulties in meditation.
Deep brain stimulation	It is possible that deep brain stimulation alters mechanisms of PD symptoms compared with those without deep brain stimulation, which may affect the study results.
Expected change in PD medications or non-motor symptom medications (e.g., sleep, anxiety, and depression medications)	Changes in medication can induce changes in PD symptoms, which may confound the study findings.
Abbreviation: PD, Parkinson’s disease.	

**Table 2 medicines-06-00013-t002:** Six healing sounds Qigong exercise instruction

Movement	Sound	Body Movement and Breathing
Relaxation movement	No sound	When inhaling, lift up both arms/hands with elbows fully extended out from both sides with palms down. Lift arms to the shoulder level. Move both arms/hands horizontally to the front and then towards the chest. Exhale as arms/hands move down slowly until the end of exhalation. Repeat the breath and body movement three times. Perform this movement before Movement 1, between each movement, and after Movement 6 (a total of seven times throughout the exercise).
Movement 1	Hsu [shh]	When inhaling, lift up both arms/hands near the body to chest level, palms facing up. Then straighten the arms out to the sides. Then move the hands to the chest. Exhale as the arms/hands move down. During the slow exhalation, chant “shh”. Repeat the sound and movement six times.
Movement 2	Her [her]	When inhaling, lift up both arms/hands near the body to the chest level with the palms facing up. Begin to exhale. During exhalation, chant “her” and continue to slowly move arms/hands up to the eyebrow level. Inhale while moving arms/hands down. Convert to exhalation when hands pass the chest level and continue to move arms/hands down. Repeat the sound and movement six times.
Movement 3	Hoo [who]	When inhaling, lift up both arms/hands near the body to chest level, palms facing up. Then, begin to exhale and chant “who” while slowly moving your left hand up and right hand down in a diagonal direction until the end of exhalation. Inhale and move left hand down and right hand up to the chest level again. Convert to exhalation and chant “who” while slowly moving the left hand down and the right hand up in a diagonal direction until the end of exhalation. Repeat the sound and movement three times.
Movement 4	Sss [sss]	When inhaling, lift up both arms/hands to the chest level, palms facing up. Begin to exhale. During exhalation, chant “sss” while slowly pushing the hands forward and then down to both sides until the end of exhalation. Repeat the sound and movement six times.
Movement 5	Chway [ch-way]	When inhaling, lift up both arms/hands through the back of trunk to the front of the chest as if holding a large ball. Begin to exhale. During exhalation, chant “chway” while slowly moving both hands out over and down an imaginary ball until touching the thighs. (Bend both knees down slightly while you circle your hands down over the ball). Repeat the sound and movement six times.
Movement 6	See [see]	When inhaling, lift up both arms/hands near the body to the chest level, palms facing up. Begin to exhale. During exhalation, chant “see” (with a smile on your face) and continue to slowly lift hands straight over the head until the end of exhalation. Begin to inhale while slowly moving returning arms/hands along the same path. Begin to exhale again when the hands pass over the chest and continue to move arms/hands down until the end of exhalation. Repeat the sound and movement six times.

Throughout the entire exercise sequence, focus your mind on an important focal point, the so-called “Dan Tian” acupuncture point, which is located in the abdomen three finger widths below your belly button to establish and maintain the mind emptiness status. Note: The format of the exercise program will be the same over the 12-week intervention. The instruction is adapted from Moon et al. (2017).

